### Participant recruitment and retention

We plan to enroll 200 participants. Patients are identified through chart reviews, tumor boards, and direct referrals from oncology clinicians. With the clinician’s permission, a research coordinator contacts the patient by phone to explain the study and screen for eligibility. Written informed consent is obtained electronically via the OHSU electronic data management system (REDCap) before or at the first study visit. For patients we cannot contact prior to their first chemotherapy infusion, or who express that they are too overwhelmed for a research visit at their first infusion, we offer to delay study enrollment until the second chemotherapy cycle. Patients are not enrolled after their second chemotherapy cycle because important information about early changes in symptoms and function can no longer be obtained.

We use several strategies to retain participants in the study. One research assistant is assigned to each participant throughout the study to establish a trusting relationship between each participant and a research team member. We minimize participant burden by using home-based data collection (online surveys and passive monitoring devices) and by conducting testing visits in the clinic just prior to regularly scheduled oncology appointments. If participants do not have a scheduled post-treatment clinic visit within the desired time frame, they are asked to schedule a separate research visit at the Knight Cancer Institute. Participants are remunerated for each study visit ($25 for research visits that coincide with clinic visits or $50 for separate post-treatment research visits). Travel compensation is provided for participants who live > 30 miles from OHSU to attend separate post-treatment research visits.

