### Falls

#### Falls

Falls that occurred during the 12 months prior to enrollment are assessed retrospectively at baseline, and falls that occur prospectively are assessed at weekly intervals using in-house surveys. These surveys ask patients about the number of falls, the nature of any injurious falls, and medical care resulting from a fall during the observation period. A fall is defined as unintentionally coming to rest on the ground or at some other lower level, not due to a major intrinsic event (e.g., stroke or syncope) or overwhelming hazard [51]. An injurious fall is one that results in fractures, head injuries, sprains, bruises, scrapes, or serious joint injuries, or where the participant seeks medical care [51].

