 Each patient's intercept and growth estimates for each measure will be entered into a GMM to identify patient clusters with distinct symptom and function trajectory profiles. For each patient, a probability of belonging to each latent class will be assigned, and the highest membership probability will be used to make a final class assignment. Identification of the best-fitting model will be based on information criteria (e.g., Bayesian Information Criterion), where smaller numbers indicate a better fit, convergence (entropy > 0.80), the proportion of the sample in each latent class (not < 5%), posterior probabilities (mean probability of belonging in “most likely” class near 1.0), and the Lo-Mendell-Rubin adjusted likelihood ratio test (which is used to compare alternative models, e.g., k vs. k-1 classes) [53]. After a good fitting GMM model is found, the resulting latent classes will be described with respect to differences between initial CIPN symptom and functioning profile and change across time. Standard statistics (e.g., t-tests) will then be used to compare fall rates between the observed symptom and function latent classes. We will focus interpretation on effect sizes and 95% CIs. Beyond examining fall rates across the study time course, we will also explore survival models to predict time to first fall. Kaplan Meier models, Mantel-Cox log-rank tests and generalized Wilcoxon-Breslow tests will be used to evaluate differences in the distribution of time to first fall. Multivariate hazard ratios with 95% CIs and Wald χ2 statistics will be calculated from Cox models with Schoenfeld residuals used to test proportional hazards assumptions.

*Hypothesis 2.1. Sociodemographic (e.g., age, sex, comorbidities, body mass index), clinical (e.g., type of chemotherapy, # of chemotherapy cycles and/or cumulative dose of chemotherapy, disease stage, other symptoms), and mobility measures (gait and balance) can be used to predict distinct trajectories of change in neuropathy symptoms and functioning.*

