### Sample size/power calculation

Although simulation methods are available to help estimate sample size for

GMM, this requires known values for all model parameters and is not defensible given the unknowns in this domain. With 2 symptom measures (severity and interference) and 6 function measures in our most complex GMM model, however, our n-to-items ratio meets conservative sample size recommendations for related approaches (20:1) [60] and would require 160 complete cases. To maximize statistical power we will fit parsimonious models after extensive preliminary associative analyses. Regarding class comparisons, assuming 80% power, two-sided α of 0.05, and 2 equal groups, we will be able to detect small-medium sized differences in fall rates and other continuous variables between groups (Cohen’s *d* = 0.40). For categorical variables, we will be able to detect small-medium effects (w = 0.25) for cross-tabulation tables with as many as 4 degrees of freedom. Evaluable data on 200 participants is a feasible number and will allow us to address each aim while accounting for up to ~ 20% attrition.

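### Fall rates are to be compared between latent classes with t-tests and Cohen's d; for counts over unequal follow-up the 95% intervals become unreliable when classes are unequal in size, and no person-time model is named

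*Protocol article*

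**What the plan says.** The Specific analysis plan (Hypothesis 1.2) assigns each patient to the most likely latent class and then says: "Standard statistics (e.g., t-tests) will then be used to compare fall rates between the observed symptom and function latent classes". The next sentence sets the reporting basis: "We will focus interpretation on effect sizes and 95% CIs". The same section accepts a class solution as long as no class holds less than 5% of the sample. It adds exploratory time-to-first-fall analyses (Kaplan-Meier, log-rank, Cox).

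The Sample size/power calculation section confirms how fall rates are viewed. "assuming 80% power, two-sided α of 0.05, and 2 equal groups", it states, "we will be able to detect small-medium sized differences in fall rates and other continuous variables between groups", with Cohen's d = 0.40.

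The Falls section describes a count outcome: "falls that occur prospectively are assessed at weekly intervals using in-house surveys", and the surveys ask how many falls occurred. It also records a baseline history: "Falls that occurred during the 12 months prior to enrollment are assessed retrospectively at baseline".

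Observation time varies by design. The treatment phase follows each patient's own schedule and is followed by one year of recovery (Procedures). Entry may be postponed to the second cycle (Participant recruitment and retention). About 20% attrition is allowed for (Sample size/power calculation). No count model, offset or person-time weighting is named for falls.

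**The concern.** A fall rate is a count divided by an exposure. Most patients will have none or few falls, and the variance grows with the mean. Three consequences follow for a t-test on per-person rates.

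- **Weighting.** One fall in 4 weeks is a rate of 52/4 = 13 per year. It enters with the same weight as a rate measured over the full course, although it is far less precise.
- **Variance.** The class that falls more also has the larger variance. If it is also the smaller class, a pooled standard error is too small.
- **Scale.** Cohen's d for such data depends on dispersion and follow-up as well as on the difference in rates, so it tells a clinical reader little about fall risk.

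Because the plan interprets this comparison through its confidence intervals, their coverage is the property at stake.

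**Working it through.** **1. The plan's own figure.** For two equal groups, two-sided α 0.05 and 80% power, n per group = 2(1.960 + 0.842)²/0.40² ≈ 99 (noncentral t: 99.1, so 100). With 200 evaluable the detectable d is 0.398, so the stated 0.40 reproduces. With 200 evaluable in unequal classes it becomes 0.498 (20/80), 0.664 (10/90) and 0.913 (5/95).

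**2. Assumed inputs.** The article gives no fall rate, dispersion or follow-up distribution. A negative binomial count with rate λ, time t and dispersion k has per-person rate variance λ/t + kλ². Take k = 2 (gamma shape 0.5), t = 1.4 years, and 1.2 against 0.6 falls per year.

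- High class: 1.2/1.4 + 2(1.2²) = 3.737
- Low class: 0.6/1.4 + 2(0.6²) = 1.149
- Low class followed for 4 weeks only (t = 4/52): 0.6/0.0769 + 0.72 = 8.52, about 7.4 times the full-course variance, yet equally weighted

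**3. Pooled interval by hand, N = 200, smaller class falling more.** The true variance of the difference is v₁/n₁ + v₂/n₂. The pooled estimate targets s²(1/n₁ + 1/n₂), with s² = [(n₁−1)v₁ + (n₂−1)v₂]/198. Approximate coverage is 2Φ(1.972 × SE ratio) − 1.

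| Split | True variance | Pooled variance | SE ratio | Approx. coverage |
|---|---|---|---|---|
| 100/100 | 0.0489 | 0.0489 | 1.00 | 95% |
| 40/160 | 0.1006 | 0.0518 | 0.72 | 84% |
| 20/180 | 0.1932 | 0.0776 | 0.63 | 79% |

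If the smaller class falls less, the error reverses. At 20/180 the true variance is 1.149/20 + 3.737/180 = 0.078, the pooled variance about 0.194, and the interval is too wide.

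**4. Simulation over a range** (6,000 runs per scenario; N = 200 and 160; k = 1, 2, 4; rates 1.2 v 0.6 or 1.5 v 0.5; follow-up 1.2-1.6 years; 20% leaving early; smaller class at higher risk; class membership known).

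| Smaller class | Pooled t coverage | Welch coverage | Welch type I error at equal rates |
|---|---|---|---|
| 50% | 93-95% | 93-95% | 4-5% |
| 30% | 82-90% | 91-95% | 5-6% |
| 20% | 74-86% | 88-94% | 6-8% |
| 10% | 65-82% | 85-92% | 8-14% |
| 5% | 60-80% | 77-90% | 11-21% |

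Pooled-t type I error at equal rates was 4-5% throughout.

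Runs at N = 160 with 0.6 falls per person-year, gamma shape 0.5 and 20% early withdrawal gave the same pattern. Pooled coverage was 85-86% (rate ratio 2) and 77-80% (ratio 3) with a 20% class, and 80-82% and 68-71% with a 10% class. Welch covered 86-92%.

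**5. Negative binomial with log person-time offset.** Coverage was 92-97% across the runs (classes of 50%, 20% and 10%). Power at N = 200, 1.2 v 0.6, k = 2:

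| Split | Pooled t | Welch | Negative binomial |
|---|---|---|---|
| 50/50 | 77% | 77% | 79% |
| 20/80 | 66% | 40% | 62% |
| 10/90 | 50% | 15% | 39% |

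At N = 160, equal classes and ratio 2, power was 55% for the t-test and 64% for the negative binomial model.

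**6. What d = 0.40 means here.** With the variances of step 2 and equal classes, 1.24 v 0.60 falls per year gives d = 0.64/√[(3.961 + 1.149)/2] = 0.40. Under these assumptions the effect labelled small-medium is a rate ratio of about 2.1.

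**The case against.** Several points on the other side stand.

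- **Equal classes.** This is the only allocation the power statement uses, and there the t interval is close to nominal. A reader might infer that the intervals are wrong in general; they are not.
- **Validity and power.** The pooled t-test keeps its type I error near 5%, and in unequal classes the count model has no consistent power advantage. A claim of lost power holds only for equal classes.
- **Where the result is expected.** One might say that coverage fails exactly where the study expects its finding. The article does not predict a small high-risk class; 5% is a floor for accepting a model, not a forecast.
- **Raw counts.** Ignoring exposure altogether would bias the comparison if withdrawal differed by class, but the text says fall rates, so that reading is not supported.
- **Fall history.** It is tempting to call the unadjusted comparison an error because prior falls are collected. Hypothesis 1.2 is a descriptive contrast between classes, and adjustment asks a different question. The Confounding section promises covariates in the longitudinal and latent class models, and a multivariable Cox model is planned. Neither is stated to cover this comparison or names fall history, but the benefit of adjusting cannot be computed from the article.
- **Favourable set-up.** The simulated data follow the recommended model, with class membership known. Coverage near 95% is therefore a best case.

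It can also be said that the t-test is only an example, in a condensed article whose full analysis plan may name another model. That softens the point without removing it: the t-test is the only method named, and the power statement independently treats fall rates as continuous. The Cox analyses handle unequal follow-up, but they are exploratory and use only the first fall.

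**Conclusion.** The point holds in a conditional form and is a should-fix. The named method does not suit counts over unequal time, and equal classes cannot be guaranteed when the plan accepts a 5% class. If the smaller class falls two to three times as often, a nominal 95% pooled t interval covers about 70-86% with a 10-20% class. Choosing Welch does not settle the matter: it covers about 86-92% and rejects too often in small classes when rates are equal. With two equal classes the interval is adequate and the count model's gain is some power.

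These sizes rest on assumed inputs (about 0.6 falls per person-year, gamma shape 0.5, 20% early withdrawal, known classes). Across the wider range tried, pooled coverage with a 10-20% class ran from 65% to 86%. The weighting problem and the mismatch of scale do not depend on those figures.

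**What to change.** For Hypothesis 1.2, name negative binomial regression (or Poisson with robust standard errors) of fall count on class as the fall-rate comparison, with offset log(weeks with a completed fall survey). Report rate ratios with 95% CIs.

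Restate the detectable effect as a rate ratio, for equal and for unequal classes, with the assumed fall rate, dispersion and follow-up written down.

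Beside the unadjusted contrast, report a secondary model adjusted for the 12-month pre-enrolment fall count and age, labelled as answering a different question.

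The cost is a change of wording and a routine model; all the data are already collected. The drawback is that the effect is reported as a rate ratio and is no longer on the Cohen's d scale used for the other class comparisons.

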**Discussion:**

Identifying simple, early predictors of functional decline and fall risk in adults with cancer receiving neurotoxic chemotherapy will help identify individuals who would benefit from early and targeted interventions to prevent CIPN-related falls and disability.

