## Methods

### Study aims and hypotheses

Our study aims and hypotheses are three-fold: (1) Characterize the variability in trajectories of CIPN symptoms and physical functioning in patients across treatment and 1 year of recovery. We hypothesize that there will be significant congruence between worsening CIPN symptoms and declining physical activity, mobility, and self-reported physical functioning and disability; (2) Identify 2 or more distinct trajectories of change in symptoms and functioning associated with significant differences in fall rates. We hypothesize that we can identify 2 or more distinct trajectories of CIPN and physical functioning associated with falls; and (3) Identify the simplest set of predictors that identify patients at risk for CIPN-related functional decline and falls. We hypothesize that some combination of patient characteristics (e.g., age, sex, comorbidities, body mass index), chemotherapy features (e.g., chemotherapy drug class, number of chemotherapy cycles, cumulative chemotherapy dose), and mobility measures (gait, balance) will predict distinct trajectories of change in CIPN symptoms and physical functioning [9, 19, 20].

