**Fig. 1 Fig1:**
[figure not shown]
Data collection timeline. Data are collected in the clinic and at home. Participants complete objective neuropathy and performance assessments at chemotherapy infusion visits (C1, C2, C3…) every 4–6 weeks and at follow up oncology visits (R1-R4) every 3 months during the first year of recovery. At home, participants wear wearable devices for 4–7 days following each clinic assessment and complete weekly electronic surveys throughout the study

Clinic-based data collection occurs during chemotherapy according to each patient’s treatment schedule and post-chemotherapy at quarterly intervals for 1 year. The baseline clinic assessment occurs before the first or second chemotherapy cycle, and then assessments are repeated every 4–6 weeks (coincident with the treatment schedule) until the final chemotherapy infusion. CIPN and performance measures are taken during clinic visits before chemotherapy administration. Post-chemotherapy (i.e., recovery), clinic assessments are performed with routine follow-up care at approximately 3-, 6-, 9-, and 12-months post-chemotherapy.

Home-based data collection consists of web-based surveys and wearable devices. Survey invitations are sent via SMS or email according to individual preference. Brief symptom and fall surveys are administered weekly during the study. More detailed physical functioning and disability surveys are administered at time points coinciding with clinic assessments. At the end of each clinic assessment, participants receive wearable devices that measure physical activity and gait quality passively and unobtrusively in their homes. Participants are asked to wear the devices for at least 4 of the next 7 days and at least 6–8 h per day during waking hours. After 7 days, participants mail the devices back to OHSU in pre-paid, pre-addressed shipping boxes or return them to study staff at their next clinic assessment.

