#### Handling missing data

The mixed-effects growth models will be estimated with maximum likelihood, which utilizes all available outcome data for each participant without removing participants due to missingness [57]. For the GMM stage, full-information maximum likelihood (FIML) estimation will be used to handle data that is missing completely at random (MCAR) or missing at random (MAR). For data that are MAR, variables related to the missingness will be included using the auxiliary command in Mplus (i.e., to allow unbiased parameter estimation under MAR) while not including them in the data analysis model [58]. These approaches will allow the analysis of the proposed aims in the case of patient withdrawal, maximizing statistical precision and power.

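### The time-to-first-fall analysis, on its natural reading, groups patients by a class built partly from post-fall data, so its hazard ratio cannot be read as prediction

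*Protocol article*

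**What the plan says.** The first aim (Study aims and hypotheses) is to "Characterize the variability in trajectories of CIPN symptoms and physical functioning in patients across treatment and 1 year of recovery". Clinic data run to the end of that year: "clinic assessments are performed with routine follow-up care at approximately 3-, 6-, 9-, and 12-months post-chemotherapy" (Fig. 1 and the text after it).

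Under Handling missing data, the growth model "utilizes all available outcome data for each participant without removing participants due to missingness". No cut-off at a first fall or at any other time is given. Under Specific analysis plan, each patient's "intercept and growth estimates for each measure will be entered into a GMM", and then "the highest membership probability will be used to make a final class assignment". The result is one fixed class per patient.

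The Falls section says that "falls that occur prospectively are assessed at weekly intervals using in-house surveys", so the event is recorded over the same period as the trajectories.

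After the comparison of fall rates between classes, the plan adds "we will also explore survival models to predict time to first fall". It lists Kaplan-Meier, log-rank and Wilcoxon-Breslow methods, and Cox hazard ratios with a Schoenfeld check. It mentions no landmark, no restriction to pre-fall data, no time-dependent covariate and no joint model.

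**The concern.** A survival comparison treats its groups as known when the clock starts. Here the group is known only after the last assessment, and the event falls inside the interval used to form it. A fall, above all an injurious one, can plausibly lower activity, balance and self-reported function. Those post-fall values steepen the fitted decline and can move the patient into the declining class. A hazard ratio above 1 could then arise with no effect of trajectory on falls.

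The safeguards in the plan do not address this. Confounder adjustment does not remove reverse causation, likelihood-based estimation deals with missing data, and Schoenfeld residuals test proportional hazards.

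The order of events matters to this study. The article's Discussion argues that a longitudinal design can separate causes from co-occurring problems and show when early intervention is best timed. Among the analyses listed, time to first fall is the one that addresses when falls happen.

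**Working it through.** **The plan's own figure.** The article gives no event count, hazard ratio or power for time to first fall. Its nearest figure is d = 0.40 for fall rates (80% power, two-sided 0.05, two equal groups). Per group, n = 2(1.96 + 0.8416)²/0.40² = 2 × 7.849/0.16 = 98.1, rounded up to 99, or 198 in total. This reproduces with 200 evaluable patients, but it has no bearing on the timing of the covariate.

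**Order of information.**

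| Item | Period covered |
|---|---|
| Measurements that form the class | Baseline to 12 months after chemotherapy |
| Class assignment | One fixed value, known after the last measurement |
| First fall | Any week of the same period |

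For every patient with an assessment after a first fall, the class uses post-fall data.

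**Simulated size, design 1.** All inputs except the 160 complete cases and the 12-month recovery are assumptions. There are 5 months of chemotherapy, nine visits, and 25% or 40% of patients with a fall. First falls are independent of true class (true HR = 1). A first fall permanently lowers later function by 0, 0.5 or 1.0 between-patient SD. Two classes are formed from individual slopes, with a Cox model and 500 replicates. The landmark version forms classes from data up to month 5 and counts later first falls among the fall-free.

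| Fallers | Drop (SD) | Whole-period: median HR, p<0.05 | Landmark: median HR, p<0.05 (replicates kept) |
|---|---|---|---|
| 25% | 0 | 1.00, 6.0% | 1.01, 4.1% (439) |
| 25% | 0.5 | 1.31, 12.6% | 1.05, 3.7% (433) |
| 25% | 1.0 | 2.17, 68.8% | 1.06, 5.9% (286) |
| 40% | 0 | 1.01, 5.4% | 1.01, 6.6% (471) |
| 40% | 0.5 | 1.26, 15.4% | 1.00, 6.3% (447) |
| 40% | 1.0 | 1.87, 67.4% | 1.05, 5.7% (315) |

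Between 29 and 214 of the 500 landmark replicates were dropped per setting, because a class had fewer than 2 events or the fit failed.

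**Simulated size, design 2.** Here N = 200, with 17 months, nine visits, 0.8 falls/year, gamma frailty of variance 1, the worst quarter of slopes as the declining class, and true HR = 1.

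| Effect of a fall on later function | HR at 0.1 / 0.2 / 0.3 SD | p<0.05 |
|---|---|---|
| Each drop lasts 3 months | 1.04 to 1.09 | 4% to 9% |
| First fall only | 1.12 / 1.26 / 1.46 | 11% / 22% / 45% |
| Every fall, permanent and cumulative, slope SD 1.0/year | 1.19 / 1.44 / 1.80 | 14% / 41% / 79% |
| Every fall, permanent and cumulative, slope SD 0.5/year | 1.42 / 1.88 / 2.39 | not tabulated |

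A separate run with drops from every fall gave 1.38 / 1.90 / 2.52, with 35% / 85% / 99% false positives. Landmark classes in that run gave HR 0.98 to 1.02 and 4% to 6%.

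**Events lost to a landmark at month 5** (200 patients, 0.8 falls/year, t in years).

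- With frailty, P(fall by t) = 1 − 1/(1 + 0.8t). At 5/12 this is 1 − 1/1.333 = 0.250 (50 patients). At 17/12 it is 1 − 1/2.133 = 0.531 (106 patients). Events left: 106 − 50 = 56. Loss: 50/106 = 47%.
- Without frailty, P = 1 − exp(−0.8t). At 5/12 this is 0.283 (57 patients). At 17/12 it is 0.678 (136 patients). Events left: 136 − 57 = 79. Loss: 57/136 = 42%.

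With similar class proportions, the confidence interval for the log hazard ratio widens by about √(106/56) = 1.38 or √(136/79) = 1.31.

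**The case against.** The survival models are introduced as exploratory and come after the fall-rate comparison. The second aim and Hypothesis 1.2 claim only that classes are associated with fall rates, and a concurrent association does not need class to come first. This stands, and it sets the severity.

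A reader might infer that the study's main clinical message is at risk. The documents do not support that. The abstract's promise of "Identifying simple, early predictors of functional decline and fall risk" belongs mainly to the third aim. Hypothesis 2.1 serves that aim by relating patient, treatment and mobility measures to class membership, not class to later falls. The third aim does mention falls, so the link is not empty, but it does not run through the Cox model alone.

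A reader might also infer a large and nearly certain false positive. The highest figures need permanent drops that add up with every fall, or one very large drop. Short-lived effects leave the error rate close to nominal.

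The article does not say outright that class is the Cox covariate, and a condensed article may leave covariates and time origin to a fuller plan. However, class is the only grouping defined in that paragraph, and a log-rank test needs groups. The article itself fixes how class is built, which tests are used and for what purpose, and that combination does not support prediction.

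Early withdrawal could also pull a patient's estimates towards the average trajectory. That was not quantified, and nothing here rests on it.

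**Conclusion.** The point holds as a should-fix. On its natural reading, the plan uses a class that includes post-fall measurements as if it were known at time zero, so the hazard ratio cannot be read as prediction. The direction of the bias follows from the design if falls worsen later function. Its size does not follow from the documents. With a true hazard ratio of 1, the simulated range is about 1.0 with no effect or a short-lived one, about 1.1 to 1.5 when only the first fall lowers function by 0.1 to 0.3 SD, and about 2 or more with large, or permanent and cumulative, drops. These figures assume 5 months of chemotherapy, the stated fall frequencies, and classification on a single slope; the plan's most complex model has 2 symptom and 6 function measures. If falls leave later function and its measurement unchanged, the simulated bias disappears. The comparison of fall rates stands as a statement of association.

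**What to change.** 1. Keep the whole-period class comparison, including its Kaplan-Meier and Cox output, but describe it as concurrent association and remove *predict*. State whether class is the Cox covariate.
2. For any predictive statement, add one of these as a supplementary analysis:
   - a landmark analysis, with class or slopes from data up to the last infusion and first falls counted afterwards among patients still fall-free, adjusted for age and falls in the year before enrolment;
   - trajectory values up to each time as time-dependent covariates, or a joint model. Either also keeps the falls during chemotherapy, which matter to the study's question of when risk develops.

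No new data are needed. The cost is one extra model. The landmark version would lose about 42% to 47% of first-fall events at an assumed 0.8 falls/year, and small classes may have too few events for a stable fit. It should therefore not replace the whole-period comparison, and it should be reported with its wider confidence interval.
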